### Plans to promote participant retention and complete follow-up {18b}

Retention is critical to the success of our study, whose aim is to assess if the TreC Diabete platform will positively impact on clinical outcomes of T2DM subjects. Participants are invited to complete questionnaires and to undertake blood tests regardless of their level of engagement with the App. Moreover, participants will provide informed consent for the researcher team to access HIS database data, enabling them to collect information on clinical outcomes even if participants are not going to complete the study as planned. The regular visits planned at the Diabetic Clinics will allow nurses and clinicians to invite participants to use the App more frequently whenever the App is used in a suboptimal way. Lastly, we expect that frequent reminders will help the intervention group participants to engage with the App. No study within a trial (SWAT) was planned for our study.

### Data management {19}

#### Data forms and data entry

 Data are entered electronically in the Microsoft Access (version 2007) programme package. The file containing all the information is protected by a password and shared only within the research team. The HIS database, from which clinical outcomes data and other indicators are going to be collected, will only be accessed at the participating sites (Hospitals of Rovereto and Trento) to ensure data security. Each member from the staff has a personal password and can only access the HIS database under specific authorisations. Participant files will be maintained in storage for a period of 3 years after completion of the study.

#### Data transmission and editing

 Data integrity is guaranteed through different approaches, ranging from valid value assessment, range and consistency checks, when data entry is implemented, where the different pieces of information will be retrievable for viewing through the data entry system. Specific privileges are assigned to users in line with their user identification code and password.

#### Data discrepancy inquiries and reports to core coordinating centres

 A system to detect missing data or specific errors is implemented, and the identified Data Manager is in charge of cross/check the original forms and other sources—if needed—in case of inconsistency, and finally amending the form accordingly. Each inquiry received will be managed; otherwise, the queried item will not be available for closure.

#### Security and back-up of data

 Each coordinating centre will have possibility to access only to the data pertaining to the centre itself, whilst access’ passwords will be changed on a regular basis in line with internal procedures. A daily back-up of the primary database will be guaranteed, whilst back-ups of periodic data analysis files will be stored. Once the study is completed, the final database is available on the server of APSS. After 3 years, the data will be deleted or anonymised.

#### Study status reports

 Monthly reports with information on missing data will be produced for review and management purposes.

#### Description of hardware

 Personal computers connected with APSS server and intranet network, which can be accessed through a unique username and password.

### Confidentiality {27}

Information collected through the study is stored securely in locked cabinets at the study sites. Locked cabinets are located in rooms which are accessible only by healthcare and research staff members. Any form containing personal identifiers are located separately from the study records forms containing the subjects’ unique code number through pseudonymisation techniques. Databases used for data collection are secured with personal passwords and can only be accessed by the authorised research staff.

### Plans for collection, laboratory evaluation and storage of biological specimens for genetic or molecular analysis in this trial/future use {33}

Biological specimens will not be used for future search. Blood tests are carried by nurses of the Trust as outlined in the protocol. Once the results are reported on HIS, blood samples are destroyed.

## Statistical methods

### Analysis primary and secondary endpoints {20a}

The analyses of the primary and secondary endpoints will be performed based on the intention-to-treat and as per-protocol approaches. Continuous variables of the two groups will be presented as mean, SD and quartiles, whilst categorical variables will be presented as percentages.

The normality of the distributions is determined by using the normality test of Kolmogorov–Smirnov. To compare the differences between the two groups for continuous outcomes, Student’s *T* test will be used. If the assumption of normality of data distribution does not hold, Wilcoxon’s rank sum test will be used. For repeated measures of continuous variables for which there is an assumption of normality of data distribution, the one-way ANOVA test will be used. If the assumption of normality does not hold, the Friedman test will be used instead of the one-way ANOVA test.

Chi-squared test will be used for categorical outcomes. SAS 9.4 (SAS Institute Inc.) will be used to conduct analyses. For all tests, the significance level is set to 0.05 (2-sided). Professional statisticians ([name]) will conduct all analyses.

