### Eligibility criteria {10}

Participants must meet at randomisation all the inclusion criteria and none of the exclusion criteria listed in Table 1.

**Table 1 Tab1:** Inclusion and exclusion criteria

Inclusion criteria	Exclusion criteria
• Being diagnosed with T2DM; • Aged ≥ 18 and ≤ 85 years old; • Having an HbA1c level > 7% (53 mmol/mol) and < 12% (108 mmol/mol); • Being able to walk without walking aids; • Having provided written informed consent; • Having a smartphone or a tablet and being able to download the App that will be used to insert the required data	• Having a BMI < 18 kg/m^2^ and > 45 kg/m^2^; • Having a sBP < 100 or > 200 mmHg and/or dBP < 50 or > 120 mmHg; • Being diagnosed with a stage 5 CKD^a^ • Being diagnosed with a NYHA stage IV; • Poor collaboration (i.e. unwilling to modify the actual plan of control and therapy, even if not ideal) for which adherence to the study is unlikely • Having no possibility of using a smartphone or a tablet • Having medical conditions affecting the study participation (i.e. life expectancy < 1 year)

*Abbreviations*: *BMI* body mass index, *CKD* chronic kidney disease, *dBP* diastolic BP, *HbA1c* glycated haemoglobin type A1c, *NYHA* New York Heart Association, *T2DM* type 2 diabetes mellitus, *sBP* systolic BP

^a^based on the glomerular filtration rate according to the CKD-Epidemiology Collaboration equation < 15 ml/min/m^2^ accounting for individual body surface [20]

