### Outcomes {12}

#### Primary outcome measure

Difference in the participants’ HbA1c level between the two arms at 12 months. Blood tests, including HbA1c level, are carried out by qualified nurses and processed by the local analysis laboratory. Blood tests results are automatically registered on the Hospital Information System (HIS) and reviewed by clinicians and research staff involved in the study.

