### Sample size {14}

The sample size was calculated on the basis of the primary hypothesis (Hb1Ac levels are likely to decrease more in the subjects of the intervention group than for the subjects of the control group at 12 months). A lower variability around the HbA1c mean level is also expected for the subjects in the intervention group when compared to the HbA1c mean level for the subjects in the control group. It was assumed that at 12 months, the mean Hb1Ac level will be 49 (SD ± 3) mmol/mol in the intervention group and 52 (SD ± 7) mmol/mol in the control group. In order to achieve a power of 80% and to keep the significance level at 5%, the sample size was calculated to be 102 (51 in each group) by using Open Epi (a freely accessible software, https://www.openepi.com/Menu/OE_Menu.htm) as depicted in Fig. 1 below. Assuming 20% of drop-out, the required sample was calculated as 120.

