## Assignment of interventions: allocation and blinding

### Sequence generation {16a}

Stratification is applied by centre (Rovereto and Trento). Participants are randomised (block randomisation with block size of 10) to either the intervention or control group on a 1:1 basis.

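### The primary 12-month HbA1c comparison is fixed as an unadjusted two-sample test: valid, but it gives up precision that baseline HbA1c and centre could supply

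*Protocol article*

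**What the plan says.** Under Primary outcome measure, the article defines the endpoint as the difference in "HbA1c level between the two arms at 12 months". This is a comparison of levels, not of change from baseline.

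Under Analysis primary and secondary endpoints {20a}, the rule beginning "To compare the differences between the two groups for continuous outcomes" assigns Student's t test. The alternative, introduced by "If the assumption of normality of data distribution does not hold", is the Wilcoxon rank-sum test. The one-way ANOVA and Friedman tests are reserved for repeated measures. None of these is given a baseline covariate or a centre term, and the section on non-adherence and missing data {20c} adds none.

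Two other parts of the article bear on this:

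- Table 4 schedules HbA1c before T0 as well as at 3, 6, 9 and 12 months. Eligibility (Table 1) itself requires a value above 53 and below 108 mmol/mol, so each randomised participant should have one.
- Sequence generation {16a} states "Stratification is applied by centre (Rovereto and Trento"), with blocks of 10.

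**The concern.** Entry HbA1c may span 55 mmol/mol (108 − 53), while the trial is sized to detect a difference of 3. If baseline predicts the 12-month value, the unadjusted test leaves that predictable part of the between-patient variation in the error term. Randomisation balances centre by design, but the analysis does not use that balance. If centre is prognostic, the standard error is then somewhat too large.

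What is at stake is the margin of a trial designed at 80% power. At the plan's own 20% loss the unadjusted test falls slightly below that level, and adjustment could recover the shortfall without recruiting anyone.

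**Working it through.** **Inputs from the article.** Sample size {14} assumes that "the mean Hb1Ac level will be 49 (SD ± 3) mmol/mol in the intervention group" and 52 (SD 7) in the control group: difference 3, 80% power, 5% significance (two-sided, per {20a}), 51 per group, 120 in total for 20% drop-out. Evaluable after that loss: 120 × 0.8 = 96, or 48 per arm.

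**Input assumed.** The correlation r between baseline and 12-month HbA1c is not in the article. The range taken is 0.3 to 0.7, the same in both arms.

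**Step 1: reproduce the plan's figure.** n per arm = (3² + 7²)(1.96 + 0.84)² / 3² = 50.6 with unrounded normal quantiles, rounded up to 51. This matches the article, so the sample size was calculated for an unadjusted comparison.

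**Step 2: unadjusted power at 48 per arm.** Standard error = √((9 + 49)/48) = 1.099, so 3/1.099 = 2.73. Power is about 77% by the unequal-variance non-central t (78% by the normal approximation). With SD 7 in both arms the standard error is √(98/48) = 1.429 and power is 55%.

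**Step 3: residual variance under a common-slope ANCOVA.** Per SD of baseline, the slope is 3r in the intervention arm and 7r in the control arm; with equal arms the common slope is 5r. Residual variances are then:

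- intervention: 9 − 2(3r)(5r) + 25r² = 9 − 5r²
- control: 49 − 2(7r)(5r) + 25r² = 49 − 45r²
- sum: 58 − 50r²

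With SD 7 in both arms the slopes agree and the sum is 98(1 − r²).

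**Step 4: adjusted power at 48 per arm, difference 3, two-sided 5%.**

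| r | Sum, SDs 3/7 | Fall from 58 | Power | Fall from 98, SDs 7/7 | Power |
|---|---|---|---|---|---|
| none | 58 | – | 77% | – | 55% |
| 0.3 | 53.5 | 8% | 80% | 9% | 59% |
| 0.5 | 45.5 | 22% | 86% | 25% | 67% |
| 0.6 | 40.0 | 31% | 90% | 36% | 74% |
| 0.7 | 33.5 | 42% | 94% | 49% | 83% |

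A simulation of ANCOVA with arm SDs 3 and 7 (4,000 runs per setting) gives 79%, 86% and 94% at r = 0.3, 0.5 and 0.7, against 76% to 78% for the t test. It agrees with the formula.

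**Step 5: chance baseline imbalance.** Baseline SD is not given; assume 7 to 12 mmol/mol. With 60 randomised per arm, the standard error of the baseline difference is 7√(2/60) = 1.3 to 12√(2/60) = 2.2, so an imbalance of 1 to 2 mmol/mol would be ordinary. Under the plan's SDs it reaches the 12-month estimate multiplied by a slope of 5r/SD: from 5 × 0.3/12 = 0.13 to 5 × 0.7/7 = 0.50. The shift is therefore about 0.1 to 1.0 mmol/mol.

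**Centre.** The article gives no between-centre variance, so its contribution cannot be calculated.

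**The case against.** The strongest reply is that nothing here is an error. The t test is valid and unbiased under randomisation, it agrees with the sample-size calculation, and a statistical analysis plan, if one exists, is the usual home for covariates. The first two parts stand. The third does not remove the point, because the article names the test for continuous outcomes instead of leaving it open.

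A reader might infer three stronger things that the article does not support:

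- **That a baseline imbalance passes whole into the result.** The endpoint is the 12-month level, so only the slope-weighted part does (step 5). The ordinary standard error already allows for that chance variation.
- **That the unadjusted confidence interval misleads.** Ignoring a stratification factor makes the test, if anything, slightly conservative.
- **That power could be computed by shrinking each arm's SD by √(1 − r²).** With SDs 3 and 7 this assumes a separate slope in each arm and overstates the gain of a common-slope model.

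It also stands that every gain rests on an r the article does not supply. At r = 0.2 the summed variance falls only from 58 to 56. Nor is the change free of cost: the test is fixed in the protocol of an ongoing trial, and ordinary ANCOVA standard errors assume the equal variances that the sample-size section expects not to hold.

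**Conclusion.** The point holds as a recommendation on efficiency, not as a fault of validity. The stated primary test ignores a baseline value scheduled for everyone and the stratification factor. With the plan's SDs, adjustment for baseline HbA1c would add roughly 3 points of power at r = 0.3 and 17 at r = 0.7. With SD 7 in both arms it would add 4 to 28 points. The direction is secure for any correlation likely in practice; the size is not, because r is assumed. The figures also assume 48 evaluable per arm, equal correlation in both arms and nothing gained from centre.

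**What to change.** Before analysts see outcome data by arm, specify the primary analysis as an ANCOVA of 12-month HbA1c on arm, baseline HbA1c and centre in all randomised participants. Use heteroscedasticity-robust standard errors, because Sample size {14} expects unequal SDs, and report the adjusted mean difference with its 95% CI. Use the same form for other continuous outcomes that have a baseline value, such as weight, blood pressure, lipids, SF-12 and DASI. Keep the unadjusted t test as a sensitivity analysis.

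The cost is one or two degrees of freedom and a documented protocol change notified to the ethics committee, as the article's section on protocol amendments {25} requires. No new data are needed. The article says that analysts are unaware of allocation and that no interim analysis is planned, so the change can be made without knowledge of the results.

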### Methods in analysis to handle protocol non-adherence and any statistical methods to handle missing data {20c}

The analysis will be conducted by “intention to treat” and “per protocol”. Given our expectation that very few patients will crossover or be lost to follow-up, these analyses should agree very closely.

Missing data will be managed according to the SAS version 9.3 MI procedure, which consists of the multiple imputation methods chosen by pattern of data missingness and type of imputed variable (SAS Institute Inc.)

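### A normality pre-test can switch the primary analysis from the mean difference in HbA1c to a rank test, although the trial is sized on means with SD 3 versus 7

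*Protocol article*

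**What the plan says.** All references are to the protocol article.

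- Primary outcome measure: "Difference in the participants’ HbA1c level between the two arms at 12 months".
- Sample size {14}: the planned values are "49 (SD ± 3) mmol/mol in the intervention group and 52 (SD ± 7) mmol/mol in the control group". The unequal SDs are deliberate: "A lower variability around the HbA1c mean level is also expected for the subjects in the intervention group".
- Analysis primary and secondary endpoints {20a}: a Kolmogorov–Smirnov test judges normality. Student's t test compares the arms on continuous outcomes. "If the assumption of normality of data distribution does not hold", Wilcoxon's rank sum test replaces it. The rule covers continuous outcomes in general and does not exempt the primary one. No unequal-variance version is named. On the level: "For all tests, the significance level is set to 0.05 (2-sided").
- Section {20c}: both intention-to-treat and per-protocol analyses are planned, with multiple imputation, "which consists of the multiple imputation methods chosen by pattern of data missingness and type of imputed variable".

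**The concern.** The sample size concerns a difference in means between arms whose variances are expected to differ by 49/9 = 5.4-fold. The analysis rule does not follow from that. Its default test pools the variances. Its fallback compares ranks, and can be read as a comparison of location only if the two distributions share shape and spread. The data decide which one is used.

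Three things are at stake:

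1. The quantity tested in the primary analysis may change after the data are seen.
2. Power for the hypothesis the trial was sized on may drop.
3. The 5% level for comparing means may not hold in some plausible settings.

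**Working it through.** **Inputs.** Means 49 and 52, SDs 3 and 7, power 80%, 51 per arm (Sample size {14}); two-sided 0.05 (section {20a}); 1:1 allocation in blocks of 10 within centre (Sequence generation {16a}). Skewness and unequal arm sizes below are assumptions, because the protocol gives neither. The pairs 54/42 and 58/38 (intervention/control) each add up to 96, which is 120 less 20% drop-out.

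**1. The planned sample size.** n per arm = (3² + 7²)(1.960 + 0.842)² / 3² = 58 × 7.85 / 9 = 50.6, rounded up to 51, total 102. The stated figure is reproduced, and it uses both variances and a difference in means.

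**2. Equal arms, normal data.** With equal n the pooled and the unequal-variance standard errors are the same: √(58/51) = 1.066. Only the degrees of freedom differ: 100 for Student, and 58² × 50 / (9² + 49²) = 67.8 for Welch. So Student's t should hold its level. Simulation with equal true means (10,000 or 20,000 trials per scenario in separate runs; Kolmogorov–Smirnov test with estimated mean and SD) gave Student 5.1%, Wilcoxon 6.0%, and the planned two-stage rule 5.0–5.6%.

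**3. How often the switch happens.** The article does not say whether normality is tested per arm or on pooled data, so both were tried, at 51/51 with perfectly normal arms and SD 3 versus 7. Tested per arm, normality is rejected in about 10% of trials. Tested on pooled data, it is rejected in 40–41% under equal means and 61–63% under 49 versus 52, because a mixture of two normals with such different spreads is not normal.

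**4. Unequal analysed arms, normal data, equal means.** True SE = √(9/n₁ + 49/n₂). Pooled SE = √[s²(1/n₁ + 1/n₂)], with s² = [9(n₁−1) + 49(n₂−1)]/(n₁+n₂−2). The approximate error rate of Student's t is the two-sided normal tail beyond 1.96 × pooled SE / true SE.

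| n₁/n₂ (intervention/control) | Pooled SE | True SE | Cut-off | Approximate error rate | Simulated Student |
|---|---|---|---|---|---|
| 54/42 | 1.058 | 1.155 | 1.80 | 7.3% | 6.8–7.5% |
| 58/38 | 1.038 | 1.202 | 1.69 | 9.1% | 9.1–9.6% |
| 38/58 | 1.203 | 1.040 | 2.27 | 2.3% | 2.3–2.4% |

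The two-stage rule gave 6.7–9.5% over 54/42 to 58/38.

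**5. Skewed data, 51/51, equal means, SD 3 versus 7.** With gamma data of skewness 1, Wilcoxon rejects in about 15% and the two-stage rule in about 12–14%. Student stays at 5.2%. Direction matters: the more variable right-skewed arm (control) has the lower median, so nearly all these rejections favour control. At this skewness, at 48/48 with normality tested per arm, the two-stage rule rejected in favour of the intervention in 1.1%, against a nominal 2.5%.

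**6. Power, 49 versus 52, 51/51.** With normal data, Student and Welch both have about 79–80%. With skewness 1, both have about 82%, while the two-stage rule has 56–64%.

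**7. No difference in mean or spread.** With SD 5.4 in both arms, the two-stage rule gave 4.7–5.3% at 51/51, for normal data and for skewness 1 alike.

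**8. Welch throughout.** With SD 3 versus 7, it rejected in 4.8–5.8% over the arm sizes and shapes tried in the main set of simulations, and in 4.6–5.6% in a second set.

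**The case against.** A fair defence has several parts.

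- **The base case is sound.** Allocation is 1:1 in blocks, multiple imputation keeps the intention-to-treat arms nearly equal, and few losses are expected. With normal data the rule then has close to 5% error. This stands. A reader might infer that the primary error rate is simply not 5%; the planned design does not support that.
- **The smaller SD is part of the expected effect.** If the App changes nothing, randomisation makes the two distributions identical and both tests keep their level, even with skewed data. This stands. The inflation needs equal means together with different spreads, plus skew or imbalance.
- **The skewed-data rejections favour control.** They do not create false claims of benefit in a superiority trial. This stands, so the cost under skewness is mainly lost power and a changed question.
- **Neither test strictly needs equal spread.** Student's t hardly needs it with equal arms, and Wilcoxon is valid as a test of identical distributions. This is correct, but Wilcoxon is then not a test of the mean difference that sized the trial.
- **Arm means would still be reported.** Section {20a} promises mean, SD and quartiles, and the article does not exclude a confidence interval. A reader might infer that the mean difference would disappear from the report; the text does not say so. What changes is the test behind the primary conclusion.
- **Details can be left to the analysis plan.** Whether normality is checked per arm or pooled, and how results are combined over imputations, may be settled there, and their absence is no fault here. The switching rule, however, is stated in the article, and an analysis plan could cure it only by replacing it.

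**Conclusion.** The point holds as a should-fix. The protocol lets the data choose the primary test, and one of the two candidates does not test the difference in means for which 51 per arm was calculated. That follows from the text and needs no simulation.

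How often the switch would occur depends on how normality is checked: about 10% of trials per arm, or 41% (equal means) to 63% (49 versus 52) on pooled data, with normal arms and the planned SDs.

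The effect on error and power is conditional. Near 5% is kept with normal data and equal arms, and also if the App affects neither mean nor spread. If the spreads differ as assumed, the level for comparing means is about 7–9.5% when the intervention arm is the larger (assumed 54/42 to 58/38), and Student's t becomes conservative when it is the smaller. This concerns mainly the per-protocol or a complete-case analysis. At an assumed skewness of 1 the level is about 12–14%, nearly all favouring control, and power falls from about 82% to 56–64%. The documents give no evidence on the skewness of 12-month HbA1c or on final arm sizes, so these figures show what could happen and are not forecasts.

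**What to change.** Remove the normality pre-test for the primary outcome. Name one comparison of mean HbA1c at 12 months that does not assume equal variances: either Welch's t test, or an analysis of covariance adjusted for baseline HbA1c (already collected, Table 4) with heteroscedasticity-robust standard errors. Combine the estimate and its standard error over the imputed data sets, and report the mean difference with its 95% confidence interval. Keep Wilcoxon's rank sum test as a sensitivity analysis only, and describe it as a comparison of distributions. Settle this before anyone sees outcome data by arm.

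The cost is a change of wording in the analysis plan. For Welch at 51 per arm, the degrees of freedom fall from 100 to about 68, and power with normal data stays at about 79%, practically the same as Student's t. No extra participants or measurements are needed.

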#### Secondary objectives

Secondary objectives include the impact of the mHealth platform use in terms of control of blood pressure and cholesterol, modification of body weight, amount of physical activity, number of hospitalisations, adherence level to prescriptions, improvements of quality of life, satisfaction and usability of the application at different follow-up times within and between groups.

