#### Secondary outcome measures

Secondary outcome measures are collected at different time point (for specific times of data collection refer to Table 4).Proportion of participants with Hb1Ac < 53 mmol/mol within the two arms;Difference in HbA1c levels between the two arms other than at 12 months;Reporting frequency and number of new hypoglycaemic episodes within the two arms;Proportion of participants reaching the targeted lipid profile (LDL level < 70 mg/dl and non-HLD cholesterol level < 100 mg/dl) and BP levels (sBP < 130 mmHg or > 140 if ≥ 65 years old);Effect on weight, lipid profile and BP levels for the App users;Effect on physical activity performed during the last 7 days prior filling in the questionnaire, for both arm participants;Number of hospitalisation events within the two arms;Number of measurements and level of physical activity with the prescribed activities (body weight monitoring, BP measurements, physical activity) within the two arms;Changes in quality of life (QoL) scores for participants of both arms;Satisfaction and usability score of the App in the intervention arm;

**Table 4 Tab4:** Time schedule of enrolment, interventions and assessments during the study period, adapted from the example template provided by the SPIRIT Group [28]

	Enrolment		Allocation		Post-allocation			Close-out	Personnel and participant involvement	Method of data collection
Timepoint	14 to 21 days prior T0	7 to 14 days prior T0	0 months	0 months (T0)	3 months (T1) (± 30 days)	6 months (T2) (± 30 days)	9 months (T3) (± 30 days)	12 months (T4) (± 30 days)		
ENROLLMENT										
** Informal study information**	x	x							Clinician	Scheduled appointment at clinic
** Eligibility screen**	x	x							Clinician or PI	Scheduled appointment at clinic
** Informed consent signed**		x							Clinician or PI and participant	Face-to-face meeting
** Allocation**			x						Research team	Face-to-face meeting
** Blood tests prescription**		x							Clinician	Face-to-face meeting
** Provide 3 copies of IPAQ questionnaire**		x							Research team	Face-to-face meeting
INTERVENTION										
** App education and instruction manual**				x					Research team	Face to face meeting
** Inform GP of participation**				x					Clinician	Through email
** Help and support with the App use**				x	x	x	x	x	Research team	Phone- email
** App (intervention) monitoring**				x	x	x	x	x	Clinician or research team	Medical dashboard

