### Participant timeline {13}

Participants will be followed for 12 months (± 30 days)—T4—starting from the allocation time (T0). Post-allocation evaluations are set to be at 3, 6 and 9 months (± 30 days)—(T1, T2 and T3, respectively). Table 4 depicts the time schedules of enrolment, interventions and assessments at different time points [32].

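### The one-way ANOVA or Friedman rule for repeated measures yields no arm or arm-by-visit effect and, read literally, ignores within-patient correlation; secondary outcomes only

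*Protocol article*

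**What the plan says.** Section {20a} of the protocol article gives two rules for continuous outcomes.

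- **Between groups:** "To compare the differences between the two groups for continuous outcomes", Student's t test is named, with Wilcoxon's rank sum test if normality fails. Nothing limits this rule to month 12.
- **Repeated measures:** "For repeated measures of continuous variables for which there is an assumption of normality of data distribution, the one-way ANOVA test will be used". The fallback reads: "If the assumption of normality does not hold, the Friedman test will be used instead of the one-way ANOVA test". No subject term, arm term or arm-by-visit term is named.

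The outcomes concerned are set elsewhere in the article.

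- The secondary objectives ask for effects "at different follow-up times within and between groups".
- One secondary outcome is "Difference in HbA1c levels between the two arms other than at 12 months".
- Table 4 schedules HbA1c, body weight, vital signs and IPAQ at baseline and at 3, 6, 9 and 12 months.
- The primary outcome is a single-time comparison: "Difference in the participants’ HbA1c level between the two arms at 12 months".

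**The concern.** The secondary objectives want within-group and between-group answers over several visits. The rule written for repeated measures serves this poorly on either reading.

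- **Literal reading.** A one-way ANOVA assumes independent observations, but up to five values come from the same patient.
- **Charitable reading.** Friedman is the usual non-parametric partner of the one-way repeated-measures ANOVA, so that version may be meant. Its only factor is time. It shows whether an arm changed, not whether the arms differ or diverge.

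The practical risk is interpretive. Table 1 requires HbA1c above 53 mmol/mol at entry, and the sample size section assumes a control mean of 52 mmol/mol at 12 months, so the plan itself expects the control arm to fall. If the repeated-measures results are arm-by-arm p values, a significant change in the App arm beside a non-significant one in the control arm may be read as an App effect. The sample size section also expects a smaller spread in the App arm (SD 3 against 7), which makes that pattern more likely even with no App effect.

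**Working it through.** **Inputs from the protocol article.** Two arms, 1:1; 51 evaluable per arm; 12-month SDs of 3 and 7 mmol/mol; planned difference 52 − 49 = 3 mmol/mol; two-sided 5% level; baseline plus four follow-up visits.

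**Assumed, because the article gives no value.** Equal within-patient correlation ρ between visits, from 0.3 to 0.8; the stated SDs held at every visit; the sizes of common falls used below.

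**1. The plan's own figure.** n per arm = (3² + 7²)(1.960 + 0.842)²/3² = 58 × 7.85/9 = 50.6, so 51 per arm and 102 in total. This agrees with the article. It concerns the 12-month comparison; no figure is stated for the repeated-measures analysis.

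**2. Literal one-way ANOVA, visit as factor, one arm, no true change.** With correlated visits, the between-visit mean square estimates σ²(1 − ρ), while the residual mean square still estimates about σ². The F ratio therefore centres on 1 − ρ instead of 1. With five visits and 51 patients the 5% critical value is F(4, 250) = 2.41. The rejection probability is about P(χ²₄ > 4 × 2.41/(1 − ρ)):

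- ρ = 0.3: P(χ²₄ > 13.8) = 0.8%
- ρ = 0.5: P(χ²₄ > 19.3) = 0.07%

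Simulation (3,000 runs) gives 0.6% at ρ = 0.3 and 0.0% to one decimal at 0.5, 0.7 and 0.8. The test is far too conservative.

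**3. What that costs.** For a fall reaching 3 mmol/mol by month 12 (1.5, 2, 2.5 and 3 at the four visits), SD 7, ρ = 0.6, 2,000 runs:

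| Test within one arm | Rejection rate |
|---|---|
| Ordinary one-way ANOVA | 21% |
| One-way repeated-measures ANOVA | 85% |
| Friedman | 76% |

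**4. Repeated-measures ANOVA and Friedman, no true change.** Type I error is 4.3% to 5.3%, so both are valid for time. The 85% and 76% in step 3 arose with the same fall in both arms and no arm effect, so such a result says nothing about the App.

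**5. Between-arm t test at each visit.** Type I error is 4.5% to 6.0% at ρ from 0.3 to 0.8. With a true 3 mmol/mol difference at every follow-up visit, SD √((9 + 49)/2) = √29 and ρ = 0.6, power is 79% to 80% at each of months 3, 6, 9 and 12. It uses one value per patient, so the within-patient correlation does no harm.

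**6. Size of the interpretive risk.** Identical true falls of 2 mmol/mol in both arms, linear or immediate, no App effect, 51 per arm, five visits, ρ from 0.5 to 0.7:

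- SDs 3 (App) and 7 (control): Friedman is significant in the App arm only in 36% to 66% of trials, and repeated-measures ANOVA in 24% to 58%.
- SD 7 in both arms: Friedman is significant in exactly one arm in 43% to 50%.

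A repeat of these simulations gave the same figures within simulation error.

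**The case against.** The strongest reply is that the two rules in section {20a} divide the work: t test or Wilcoxon for between-group questions, ANOVA or Friedman for change over time. The objectives do ask for within-group effects, and lacking an arm term is no fault in a within-group test. Much of this stands.

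- A reader might infer that the 3-, 6- and 9-month between-arm outcomes get a wrong answer or none. The documents do not support that. The HbA1c difference at those visits is a between-group continuous outcome, and the t test or Wilcoxon rule covers it validly (step 5).
- A reader might also infer a badly inflated false-positive rate. A one-way ANOVA with arm as the factor on four stacked follow-up visits would have a type I error of 2(1 − Φ(1.96/√(1 + 3ρ))), which is 21.5% at ρ = 0.5 and 26.6% at 0.7. The article describes neither stacking nor arm as the ANOVA factor, so this figure cannot be charged to the plan.
- Friedman needs complete rows, but section {20c} provides multiple imputation, and section {18b} allows clinical outcomes to be taken from the hospital system for participants who do not complete. Loss of incomplete cases is therefore not a firm objection.
- The figures in step 6 need someone to compare within-arm p values. The article does not propose this and supplies a direct between-group test. They measure a risk of misreading, not a planned inference.

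Two things remain. The method is fixed in plain words, so this is not detail left to an analysis plan, and those words name a test that is unsuitable if taken literally. Also, HbA1c, weight, blood pressure and IPAQ are at once between-group and repeated, the text does not say which rule governs them, and neither rule gives an arm-by-visit effect.

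**Conclusion.** The concern holds in a limited form and should be fixed. The repeated-measures rule is either invalid for correlated visits (size below 1%; power 21% against 85% in the example) or confined to change within an arm, with no arm or arm-by-visit effect. It affects secondary outcomes measured at several visits: HbA1c, weight, blood pressure and IPAQ. The primary 12-month comparison and its sample size do not use this rule.

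That neither test contains an arm effect needs no numerical assumption. The error rates and power depend on assumed equal correlations, on SDs held constant over visits, and on illustrative falls of 2 or 3 mmol/mol. They show direction and order of size and do not predict this trial.

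**What to change.** Replace the one-way ANOVA and Friedman rule in section {20a} with one linear mixed model for repeated measures for each outcome collected at several visits. Include arm, visit, arm-by-visit, baseline value and centre (the stratification factor), with unstructured within-patient covariance. Report the between-arm difference with its 95% confidence interval at 3, 6, 9 and 12 months. State that the primary analysis remains the 12-month comparison already specified, so that the model's 12-month estimate does not compete with it. Report any within-arm change as descriptive only, without inference about the App.

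If the present tests are kept, the minimum is to state that the repeated-measures form of ANOVA is meant, that it and Friedman describe change within an arm only, and that the t test or Wilcoxon test governs every between-arm comparison.

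The cost is a change of analysis wording and a standard procedure in SAS, the software already named. No new data, visits or participants are needed.
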